#### Primary outcome measures

An analysis of covariance (ANCOVA) model will be used to compare the final clinician administered S-STS scores between the groups, including the initial score as a covariate.

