### Study population

Patients will be recruited from six psychiatric hospitals (Dresden University Clinic, Dresden Neustadt, Berlin, Bochum, Frankfurt, Göttingen) in Germany. Specifically, patients will be recruited upon admission. All patients meeting inclusion criteria will be informed about the study by one of the investigators. Following informed written consent, randomization will be conducted by a central block design, allocating the participant to one of the two treatment groups. Figure 1 shows the trial time-line.

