As the study is a multi-center trial, randomization will be carried out by a centralized computer randomization directly after screening and obtainment of written informed consent at visit 2 (baseline). Study participants and the treating mental health team on the inpatient unit will be blinded for group assignment. A rater-training (including assessment of inter-rater reliability) will be provided before the study commences to minimize differences between centers.

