### Statistical analysis

Descriptive statistics using proportions, means and standard deviations will be reported where appropriate. All efficacy outcome measures will be analyzed on an intent-to-treat (last observation carried forward) basis and study completer basis. Results will be presented with 95 % confidence intervals where applicable. Proportions of adverse events will be summarized. All statistical tests will be two-sided using an alpha level of 0.05. Analyses will be adjusted for age and gender when there is a significant difference between the groups at baseline.

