## Discussion

Lithium has shown to have suicide-preventing effects in patients with affective disorders over the long-term course. No study has investigated whether this effect occurs at the beginning of treatment or develops after months of ongoing lithium therapy. The results of this study should indicate whether lithium leads to a decrease in suicidal thoughts and/or behavior within the beginning of the treatment (5 weeks).

There is a critical need to identify treatments that will acutely decrease suicidal ideation and/or behavior. Lithium therapy is widely available and inexpensive. The potential benefits of lithium therapy on acute suicidal ideation and/or behavior in patients with affective disorders need to be clarified.

In designing this study, we aimed to be as close as possible to a real-world clinical setting. The recruiting centers are a mix of university and community based psychiatric hospitals which represents a broad spectrum of patients with affective disorders. We are aware that the TAU condition may cause additional heterogeneity, as this can vary from center to center, or even within one center through different approaches of the treating psychiatrists.

This proposed study has several limitations: i) suicidal patients are generally excluded from clinical (especially pharmacological) trials. Therefore special attention and care is needed to minimize the risk in this high-risk population while undergoing a clinical trial. ii) Patients with acute suicidal crisis admitted to the hospital and treated with combined pharmacological and psychological treatments sometimes show a sudden improvement in terms of their suicidality, especially in those who were intoxicated at the time of admission. In the literature this effect is well-described as a suicide-cathartic effect after a suicide attempt [30]). Suicidality fluctuates in patients with depressive symptoms from the day of admission to a few days later when they usually are being informed about the study. As Davis et al. [31] stated, interpersonal support (attention from loved ones, and benefits from therapy) may be a mechanism by which a patient experiences immediate relief, and therefore decreased suicidal ideation/behavior. iii) Currently, no approved medication exists to treat suicidality. Patients may express concerns that they will be receiving a medication that is not approved for their specific symptoms and may refuse to participate.

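### The primary and secondary ANCOVAs leave out centre in a six-hospital trial that says usual care may differ by centre: a modest, avoidable loss of precision

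*Protocol article*

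**What the plan says.** - **Primary model** (Primary outcome measures): an ANCOVA will "compare the final clinician administered S-STS scores between the groups, including the initial score as a covariate". No other term is listed.
- **Further adjustment** (Statistical analysis): "Analyses will be adjusted for age and gender when there is a significant difference between the groups at baseline".
- **Secondary ANCOVAs** (Secondary outcome measures): for continuous outcomes, again only the initial S-STS score is named as covariate.
- **Centres** (Study population): "Patients will be recruited from six psychiatric hospitals".
- **Expected differences** (Discussion): "We are aware that the TAU condition may cause additional heterogeneity, as this can vary from center to center". The same sentence adds that practice may also differ between psychiatrists within one centre.
- **Countermeasure** (Power analysis and sample size calculation): "A rater-training (including assessment of inter-rater reliability) will be provided before the study commences to minimize differences between centers".
- **Allocation** (Study population): "randomization will be conducted by a central block design". How the blocks relate to centre is not described.

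**The concern.** Both arms receive TAU on top of lithium or placebo. If TAU differs between hospitals and affects suicidality, mean final S-STS will differ between hospitals for reasons unrelated to the study drug. A model without centre counts that variation as noise, which widens the standard error of the treatment effect. The article raises the possibility itself but does not carry it into the primary analysis. Rater training deals with how the scale is scored, not with how patients are treated.

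At stake is some power in a trial planned at only 80%, in a population that the Discussion describes as hard to enrol.

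**Working it through.** **Inputs from the article** (Power analysis and sample size calculation): score reductions of 4.8 (SD 5.1) on placebo and 6.7 (SD 5.8) on lithium, so the difference is 1.9; two-sided alpha 0.05; power 0.80; baseline-to-final correlation 0.3; 5% loss before the modified ITT sample. **Assumed, because the article gives no figure:** the share *s* of residual outcome variance that lies between centres, shown from 0 to 10%.

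**1. The plan's own figures.** The unequal-variance t-test (noncentral t) needs 131 per group, with power 80.1%. The ANCOVA factor gives (1 − 0.3²) × 131 = 0.91 × 131 = 119.2, hence 120. Then 120 / 0.95 = 126.3, hence 127, and 2 × 127 = 254. All reproduce.

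**2. Power of the model as written, 120 per group.**
- Mean variance: (5.1² + 5.8²) / 2 = (26.01 + 33.64) / 2 = 29.825
- Residual variance after baseline: 0.91 × 29.825 = 27.14
- Standard error: √(27.14 × 2 / 120) = 0.673
- Noncentrality: 1.9 / 0.673 = 2.825
- Power on 240 − 3 = 237 degrees of freedom: 80.3%

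**3. Power with centre added.** Residual variance becomes 27.14 × (1 − *s*) on 237 − 5 = 232 degrees of freedom. Arms are taken as balanced within each centre.

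| Share *s* | Standard error | Noncentrality | Power | n per group for 80% |
|---|---|---|---|---|
| 0 | 0.673 | 2.825 | 80.3% | 120 |
| 2% | 0.666 | 2.854 | 81.1% | 117 |
| 5% | 0.656 | 2.898 | 82.3% | 114 |
| 10% | 0.638 | 2.978 | 84.3% | 108 |

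**4. If arms are not balanced within centres.** Five centre indicators then explain on average 5/239 of the treatment indicator by chance. The variance of the effect rises by 1 / (1 − 5/239) = 1.021, and each noncentrality above is divided by √1.021 = 1.011. Power becomes about 79.5%, 80.3%, 81.5% and 83.5% at shares of 0, 2%, 5% and 10%. The break-even share is then about 2%.

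**5. If centre variation comes on top of the planning SD.** The residual variance of the model as written becomes 27.14 / (1 − *s*). Its power is 79.5%, 78.3% or 76.1% at 2%, 5% or 10%, while the centre-adjusted model keeps 80.3% (arms balanced within centres).

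**6. Type I error of the model as written.** This was simulated with six centres of 40.
- Allocation not balanced within centre: 4.8% to 4.9%, so the level holds.
- Allocation balanced within centre: 4.3% to 4.6% across separate simulations at a 5% share, and 3.9% to 4.2% at 10%.

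A direct approximation agrees with the balanced case. The true variance of the difference is proportional to 1 − *s*. The model estimates it as about 1 − *s* + (5/6)*s*, because six centre effects vary around their own mean. At 5% the effective critical value is 1.96 × √(0.9917 / 0.95) = 2.003, which gives 4.5%. At 10% it is 1.96 × √(0.9833 / 0.90) = 2.049, which gives 4.0%.

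**The case against.** **The loss may be negligible.** The Discussion is tentative: TAU may cause heterogeneity and can vary. Part of the variation it describes is within a centre, and a centre term removes none of that. A stable difference in rating level between hospitals would also show in the initial score, which is already a covariate. All of this stands. It is why the range must start at zero, where centre brings no gain and can cost just under one point of power if arms are not balanced within centres.

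**A full protocol or SAP might add centre.** That is possible, as neither is shown. But the article lists its covariates, including a conditional rule for age and gender, and centre is not among them. The point concerns a model that is stated, not a detail left open.

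**Stronger readings that the article does not support.**
- A reader might infer that a chance imbalance of arms across hospitals could be mistaken for a lithium effect. Without balancing by centre, the unadjusted standard error already covers such imbalance and the test keeps its level. With balancing, the test is conservative. Neither case gives bias or excess false positives.
- A reader might treat the silence on blocking within centre as a defect. A journal article commonly leaves that to the full protocol, so it is not one. The conservatism figures apply only if blocks are in fact formed within centre.
- A reader might want unipolar or bipolar diagnosis added as well. Nothing in the article shows how far diagnosis predicts the S-STS outcome, so the point does not extend to it.

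**Conclusion.** The point holds as a matter of efficiency. The stated models omit a design factor that the article itself links to possible outcome differences. With arms balanced within centres, including it would add about 1 point of power at a 2% between-centre share, 2 points at 5% and 4 points at 10%, and nothing at zero. The gain is somewhat smaller if arms are not balanced within centres.

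These sizes rest on an assumed share and, for the simulations, on six equal centres. The sample size of 127 per group is correctly derived and needs no change. The primary test remains valid as written. The change is worth making because it is cheap, not because the result would otherwise be unsound.

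**What to change.** Before unblinding, pre-specify centre (six levels) as a factor in the primary ANCOVA alongside treatment and initial S-STS score, and in the secondary models. The cost is one line in the model statement and five of about 240 degrees of freedom. Recruitment, visits and sample size are unaffected.

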So far little is known about the mechanism behind this effect. Neurobiological research has focused on lithium’s influence on neurotransmitters such as serotonin [9] or noradrenalin and dopamine [10]. Lithium’s influences on the cortisol stress hormone system [11], the γ-aminobutyric-acid [12], second messenger systems such as the inositol metabolism and glycogen synthase kinase 3 have also been investigated [13]. Lithium has demonstrated to have an effect on impulsivity and aggression via several pathways within the nerve cell [14, 15] which is discussed as one of the underlying mechanisms behind the anti-suicidal efficacy.

As suicide research has to deal with specific methodological difficulties the design and development of study protocols needs to be cautious. Ethical and statistical issues need thoughtful consideration.

In 2005, the worldwide first placebo-controlled randomized trial designed specifically to investigate the influence of lithium on suicidal behavior was conducted and published in 2008 by Lauterbach et al. [16]. Survival analysis showed no significant difference in suicidal acts between lithium and placebo-treated individuals (adjusted hazard ratio 0.517; 95 % CI 0.18–1.43); however, post hoc analysis revealed that all completed suicides had occurred in the placebo group accounting for a significant difference in incidence rates (*P* = 0.049). Within a treatment period of one year, no suicides occurred within the lithium group (*n* = 84) compared to three suicides within the placebo group (*n* = 83). No significant differences were found in terms of suicide attempts (seven suicide attempts each in the placebo and lithium group). To date, no study has investigated how fast this anti-suicidal effect appears. It is unclear where in the course of treatment this effect arises.

The primary aim of the present study is to determine whether lithium exerts an anti-suicidal effect through a decrease in suicidal thoughts and/or behavior within the first 5 weeks of treatment. The secondary aim of the study is to determine whether lithium influences suicidal thoughts and/or behavior through the indirect path of improving depressive symptoms, anxiety or impulsivity.

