- Male and female patients at least 18 years of age and older - Presenting with a depressive episode (MDE, uni/bipolar), moderate to severe according to DSM IV criteria - Admitted as an inpatient - Suicidal thoughts and/or behavior defined by a score ≥ 8 in the S-STS scale and a score ≥ 20 in the MADRS Scale at time of screening and baseline - Written informed consent	- Pre-treatment with lithium within the last six months before inclusion in the study - Patients after compulsory hospitalization or patients unable to understand the study protocol - Diagnosis of antisocial and/or Borderline personality disorder, alcohol and drug dependency (positive drug screening) - Contraindication following drug approval such as severe heart failure (arrhythmias), severe renal dysfunction, Addison’s disease and others - History of hypersensitivity towards components of trial medication - Pregnant or lactating women, women attempting to get pregnant, and women not practicing a reliable method of contraception

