### Power analysis and sample size calculation

A comparable study published by Khan et al. [26] of a 6-week double-blind trial in 40 patients found a score reduction of 4.8 (SD = 5.1) in the clinician administered S-STS in the placebo group, while a score reduction of 6.7 (SD = 5.8) was found among the lithium group The assumption that all lithium patients achieve a therapeutic serum-level in the current study seems to be reasonable due to the considerable higher lithium dose in comparison with the Khan et al. study. Therefore, these values have been used as estimates for the expected group difference in this study.

With an alpha level of 0.05, and statistical power of 0.8, sample size estimation for a two-sided *t*-test with unequal variances results in a required number of 131 patients per group. Nevertheless, a *t*-test has considerably less power than an analysis of covariance (ANCOVA), which will be used in this analysis. Borm et al. [27] showed for sample size n and a baseline-follow-up correlation rho, that an ANCOVA with (1-rho^2)*n subjects has the same power as the corresponding *t*-test. There is no published data on test-retest correlations of the S-STS to our knowledge; however, a recalculation of data from the “Basis-Studie Kompetenznetz Depression” [28] with 1014 naturalistically treated depressed patients showed correlations from 0.36 to 0.54 for the self-report S-STS between baseline and week 8. Therefore, a conservative assumption of 0.3 for the expected correlation was chosen, which yields a number of 120 patients per group. These patients will form the modified Intention to Treat (ITT) sample including all patients who will be randomized and not discontinue from the study before any efficacy measurement. A rate of approximately 5 % of randomized patients dropping out for any reason before entering the ITT sample is presumed, which results in 127 patients needed to be randomized per group. Therefore, 508 patients will be required to be screened assuming a rate of 50 % of screened patients fulfilling the inclusion criteria. We are expecting good adherence to the intervention as this will not result in major side effects. However, we anticipate that there will be about 5 % loss to follow-up, and this is accounted for in the sample size estimation.

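### Baseline MADRS, already scored before randomisation, could be pre-specified as a second covariate in the primary ANCOVA: an optional, nearly free improvement of uncertain, probably small size

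*Protocol article*

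**What the plan says.** All references are to the protocol article.

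- *Primary outcome measures*: final clinician S-STS is compared between arms by ANCOVA, "including the initial score as a covariate".
- *Statistical analysis*: the only further adjustment is for age and gender, and only if the arms differ significantly on them at baseline. MADRS is not named as a covariate anywhere in the article.
- *Table 1*: entry requires, besides an S-STS threshold, "a score ≥ 20 in the MADRS Scale at time of screening and baseline".
- *Intervention/Course*: eligibility is re-confirmed at V2, the visit at which patients are randomised and treatment starts in the evening.
- *Power analysis and sample size calculation*: the t-test requirement of 131 per group is cut to 120 through the baseline-to-final S-STS correlation, for which "a conservative assumption of 0.3 for the expected correlation was chosen".
- *Background*: a secondary aim asks whether lithium acts on suicidality "through the indirect path of improving depressive symptoms, anxiety or impulsivity".

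**The concern.** The plan already relies on covariate adjustment for precision: the step from 131 to 120 per group rests entirely on it. Having accepted that argument, it uses one baseline severity measure and leaves aside a second that is on file for every eligible patient and cannot be affected by treatment.

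There are clinical grounds to expect some added information. Everyone enrolled is in a major depressive episode, and the Discussion notes that suicidality fluctuates between admission and the days when patients are told about the study. A single baseline S-STS may therefore be a noisy measure of severity, which leaves room for another.

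Two things are at stake, both modest. The residual variance may be somewhat larger than it needs to be. And a chance difference in depression severity between the arms, so far as it predicts the outcome beyond baseline S-STS, would stay in the primary estimate; adding MADRS only after seeing such a difference would be post hoc.

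**Working it through.** **Inputs from the article.** "With an alpha level of 0.05, and statistical power of 0.8"; "All statistical tests will be two-sided using an alpha level of 0.05". The cited 6-week trial "found a score reduction of 4.8 (SD = 5.1) in the clinician administered S-STS in the placebo group", and "a score reduction of 6.7 (SD = 5.8) was found among the lithium group". The difference is 6.7 − 4.8 = 1.9.

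**The plan's own figures.**
- t-test with unequal variances (noncentral t, Welch degrees of freedom): at 131 per group SE = √[(5.1² + 5.8²)/131] = √(59.65/131) = 0.675, and power is 0.801. At 130 it is 0.798, so 131 reproduces.
- ANCOVA factor: (1 − 0.3²) × 131 = 119.2, rounded up to 120.
- Dropout of 5%: 120/0.95 = 126.3, rounded up to 127 per group, 254 in total.
- Power of the stated ANCOVA at 120 per group: SE = √(0.91 × 59.65/120) = 0.673, power 0.803.

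The last line follows the plan in applying the factor to the SDs of the score reductions.

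**Adding baseline MADRS.** Let r be the partial correlation of V2 MADRS with final S-STS, given V2 S-STS. Residual variance is multiplied by (1 − r²). The article gives no value for r, so a range is assumed. The equivalent n is 0.91 × (1 − r²) × 131, rounded up.

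| Assumed r | Variance reduction | SE reduction | Power at 120 per group | Equivalent n per group |
|---|---|---|---|---|
| 0 | 0% | 0% | 0.803 | 120 |
| 0.1 | 1% | 0.5% | 0.807 | 119 |
| 0.2 | 4% | 2.0% | 0.819 | 115 |
| 0.3 | 9% | 4.6% | 0.839 | 109 |

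**How small r could be.** With a the correlation of MADRS with final S-STS and b its correlation with baseline S-STS, and 0.3 between the two S-STS scores, r = (a − 0.3b)/√[0.91 × (1 − b²)]. Both a and b are assumed:
- a = 0.2, b = 0.5: r = 0.05/0.826 = 0.06.
- a = 0.4, b = 0.5: r = 0.25/0.826 = 0.30.

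**Cost.** With 240 patients, residual degrees of freedom go from 237 to 236. The price of a useless covariate is roughly 1/236 = 0.4% of the variance, not deducted in the table. That about cancels the gain at r = 0.06 (0.06² = 0.4%).

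**Chance imbalance.** The standard error of a standardised baseline difference is √(2/120) = 0.129, so a 1.96-SE imbalance is 0.253 SD. The residual SD of the outcome is √(59.65/2) × √0.91 = 5.461 × 0.954 = 5.21. The shift in the S-STS difference is r × 5.21 × 0.253: 0.13 points at r = 0.1, 0.26 at 0.2 and 0.40 at 0.3, which is 7% to 21% of 1.9.

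**The case against.** The strongest reply is that nothing here is wrong. The model adjusts for the baseline value of the outcome, the sample size reproduces, planned power is reached without MADRS, and under randomisation a chance imbalance neither biases the estimator nor inflates the type I error. All of this stands, and it makes the point a suggestion. The article is also a condensed document, so the absence of MADRS can be asserted only for the text shown. That text does, however, state the primary covariate.

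The benefit is also assumed. No MADRS to S-STS correlation is given, baseline S-STS may already carry most of what MADRS would add, and the entry threshold truncates the MADRS range, which would tend to weaken its correlation with the outcome. This lowers the expected gain but shows no material downside.

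Two stronger readings are tempting, and the article supports neither:

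- A reader might infer that the plan itself holds that depression drives suicidality. The Background poses this as an open question with three candidate paths. It also concerns mediation by improvement after randomisation, which does not show that baseline MADRS predicts final S-STS.
- A reader might infer that the plan expects baseline S-STS to explain only 9% of the variance. The 0.3 is called conservative and lies below the 0.36 to 0.54 found for the self-report S-STS in the cited data set. Those values mean 13% to 29% explained and power of 0.820 to 0.890 at 120 per group, so the existing covariate may already give as much headroom as MADRS would.

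One could also ask why not add baseline anxiety or impulsivity. The case for MADRS is practical: it is the other severity score that Table 1 requires of every patient before randomisation.

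**Conclusion.** The point holds as an optional improvement. The stated ANCOVA is valid and adequately powered on the plan's own assumptions; it would overstate the case to say that precision is lost or that the lithium estimate is confounded. What can be said is that some precision may be forgone. With the plan's S-STS correlation of 0.3 and an assumed partial correlation of 0.1 to 0.3, the gain is 0.4 to 3.6 percentage points of power, or about 1 to 11 patients per group, plus insurance against a visible imbalance in depression severity. If the partial correlation is near 0.06 or below, there is no practical gain. The asymmetry between a negligible cost and a possible modest gain is the whole argument.

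**What to change.** Before unblinding, state in *Primary outcome measures* that the ANCOVA of final clinician S-STS includes two continuous baseline covariates: the V2 clinician S-STS total and the V2 MADRS total. Both should be included unconditionally, whether or not the arms differ on them at baseline. The sample size need not change, since it does not rely on MADRS. The cost is one phrase of analysis text and one degree of freedom, with no new data.
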